**Methods/Design:**

We are conducting a randomised, triple-blinded, placebo controlled trial of the use of prednisolone to improve recovery from Bell’s palsy at 1 month. Study sites are 10 hospitals within the Australian and New Zealand PREDICT (Paediatric Research in Emergency Departments International Collaborative) research network. 540 participants will be enrolled. To be eligible patients need to be aged 6 months to < 18 years and present within 72 hours of onset of clinician diagnosed Bell’s palsy to one of the participating hospital emergency departments. Patients will be excluded in case of current use of or contraindications to steroids or if there is an alternative diagnosis. Participants will receive either prednisolone 1 mg/kg/day to a maximum of 50 mg/day or taste matched placebo for 10 days. The primary outcome is complete recovery by House-Brackmann scale at 1 month. Secondary outcomes include assessment of recovery using the Sunnybrook scale, the emotional and functional wellbeing of the participants using the Pediatric Quality of Life Inventory and Child Health Utility 9D Scale, pain using Faces Pain Scale Revised or visual analogue scales, synkinesis using a synkinesis assessment questionnaire and health utilisation costs at 1, 3 and 6 months. Participants will be tracked to 12 months if not recovered earlier. Data analysis will be by intention to treat with primary outcome presented as differences in proportions and an odds ratio adjusted for site and age.

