### Randomisation

Participants will be randomized in a 1:1 ratio to one of two treatment arms: intervention (prednisolone) or matched placebo. An independent statistician has generated a randomization schedule using variable block sizes, stratified by site. This schedule will be used by the central study pharmacist at RCH to undertake the blinding, labelling and distribution of the study drugs to participating sites by putting together study packs of the required drug labelled with sequential study numbers for each site and dosing instructions. Randomization will be undertaken at the site by ED and research staff by selecting the lowest numbered study pack (next pack system) from the study drug store in ED.

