#### Follow up assessment at 1 month

One month after randomization, participants will attend a visit at the study site. Where the participant is unable to attend the study site, this may be completed via videoconferencing.

A specialist clinician (a pediatric neurologist; ENT specialist; pediatrician or ED physician to accommodate site specific resources) will review the participant to: exclude an alternative diagnosis for the Bell’s palsy symptoms; determine if Bell’s palsy symptoms are still present; determine HB grade (the primary outcome) and the Sunnybrook scale of the Bell’s palsy; determine the presence of synkinesis or autonomic dysfunction using the SAQ. Facial images (video recording and still photographs) will be recorded. A questionnaire will be completed by the parent/guardian or participant (age dependent) for all participants and will elicit details on adverse events, ongoing palsy symptoms, reports of abnormal hearing, lacrimation and altered taste, date of resolution of facial palsy symptoms (if resolved) as subjectively perceived by parent and any medical contact.

The following scales and tools will be completed by the parent/guardian or participant depending on the age of the participant (varies by scale):o PedsQL and CHU-9D to assess the emotional and functional wellbeing (quality of life) of the participant.o The Harter scale to assess perceived appearance.o FPS-R or VAS to capture pain symptomso A study-specific lay translation of the HB scale

A site research assistant will collect the study drug containers from participants attending the study site for later assessment of residual volumes and return to the site pharmacy.

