### Statistical methods

#### Sample size estimation

Based on observational data [4, 14] we expect 60 % of children without prednisolone to have complete recovery at 1 month. This is in line with data from the pediatric RCT which reported complete recovery without prednisolone in 72 % at 4 months [12]. A study in adults [18] deemed an improvement of 12 % with prednisolone compared with placebo to be a clinically important difference between treatment groups. We therefore power our study to find an increase in the proportion with complete recovery from 60 % in the placebo group to 72 % in the prednisolone group. This is a conservative estimate of efficacy compared with that found in our observational pilot data [4, 14] which showed an increase in complete recovery at 1 month of 16 % in those treated with prednisolone (75 %) compared with those not receiving prednisolone (59 %). To enable us to identify an increase in recovery from 60 to 72 % or larger with 80 % power requires a study with 244 subjects in each treatment group based on a two-sided test with α = 0.05. Hence we aim to recruit 270 per group (540 in total) to allow for 10 % loss to follow-up at 1 month.

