#### Statistical analysis

Data will be analysed on an intention-to-treat basis. For the primary analysis, multiple imputation will be used to handle missing data, imputing all outcomes using a single (joint) imputation model. Imputation will be carried out separately by treatment arm to ensure that any treatment effects are maintained. As a secondary analysis, all analyses will be repeated using a complete case analysis, including all participants with data available for each outcome.

The primary outcome of complete recovery at 1 month post randomization on the HB scale (as determined by the site specialist clinician) will be presented as a proportion in each treatment group, with a comparison between the groups presented as a difference in proportions and as an odds ratio from a logistic regression model adjusted for site and age, with a 95 % CI and *p*-value. In addition, we will present the results as Number-Needed-to-Treat (NNT) and its 95 % CI. As an additional sensitivity analysis, the analysis of recovery at 1 month will be repeated assuming that all participants with missing data who have not previously been recorded as achieving complete recovery 1) have recovered, and 2) have not recovered.

All secondary outcomes will be summarized by treatment group. Binary outcomes will be presented as proportions, with comparisons between the groups presented as a difference in proportions and as odds ratios from logistic regression adjusted for site, with 95 % CIs and *p*-values. Continuous outcomes will be presented as means and standard deviations, with comparisons made using linear regression adjusted for site presented as mean differences, 95 % CIs and *p*-values. Time to recovery will be assessed using a Cox proportional hazards model censoring patients who have not recovered at 6 months, with results presented as a hazard ratio, and its 95 % CI and *p*-value. Participants who have reached complete recovery at 1 or 3 months and are not assessed at the later time points will be assumed to have complete recovery for the duration of the study. For both the primary and secondary outcome, we will repeat the analysis adjusted for age (as a continuous variable), gender, baseline severity of facial nerve dysfunction (severe = HB V and VI, non severe = HB I-IV [18, [36]) and time to treatment (≥24 vs >24–72 hours [18, [36]) as potentially important confounders.

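### Main models for the secondary outcomes adjust for site only, while the primary model adjusts for site and age: a small, unexplained mismatch that is nearly free to remove

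*Protocol article*

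**What the plan says.** All the model statements are in the protocol article, Statistical analysis.

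- **Primary outcome** (HB recovery at 1 month): reported "as an odds ratio from a logistic regression model adjusted for site and age". The abstract agrees: "primary outcome presented as differences in proportions and an odds ratio adjusted for site and age".
- **Secondary binary outcomes**: reported "as odds ratios from logistic regression adjusted for site, with 95 % CIs". The list under Secondary outcomes includes HB recovery at 3 and 6 months and Sunnybrook recovery at 1, 3 and 6 months.
- **Continuous outcomes**: "comparisons made using linear regression adjusted for site presented as mean differences".
- **Supporting repeat**, on four covariates (age, gender, initial severity of the palsy and time to treatment): "For both the primary and secondary outcome, we will repeat the analysis adjusted for age (as a continuous variable), gender, baseline severity of facial nerve" (the sentence goes on to the remaining covariate).

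A difference in proportions is also planned for the primary outcome and for every secondary binary outcome. The Randomisation section says that an independent statistician "generated a randomization schedule using variable block sizes, stratified by site"; age is not a stratification factor.

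**The concern.** HB recovery is one endpoint followed over three visits. Children who have recovered and are not assessed again are counted as recovered from then on, so readers will naturally set the three odds ratios beside each other. The main 1-month odds ratio is conditional on site and age; those at 3 and 6 months are conditional on site only. The same mismatch separates HB from Sunnybrook recovery at 1 month. Odds ratios are non-collapsible: if age predicts recovery, adding it moves the odds ratio away from 1 even when the effect is the same and the arms are perfectly balanced. Part of any change across visits or scales could then come from the covariate set.

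For the continuous outcomes the issue is efficiency. The 1-month questionnaires "will be completed by the parent/guardian or participant depending on the age of the participant (varies by scale"), so age may well account for some of the variance in those scores. It is known at baseline and the plan itself lists it as a covariate of possible importance, yet the main linear models omit it.

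**Working it through.** **1. The plan's own figure.** Sample size estimation powers the trial for an increase "from 60 % in the placebo group to 72 % in the prednisolone group", with two-sided α = 0.05, 80 % power and 244 per group.

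n = [1.960 × √(2 × 0.66 × 0.34) + 0.842 × √(0.60 × 0.40 + 0.72 × 0.28)]² / 0.12² = (1.313 + 0.559)² / 0.0144 ≈ 243.4, rounded up to 244.

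The stated figure reproduces (power 80.1 %), and this point does not affect it.

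**2. Odds ratio without age.** (0.72/0.28) / (0.60/0.40) = 1.714, log 0.539. With 244 per group, the standard error of the log odds ratio is √[1/(244 × 0.60 × 0.40) + 1/(244 × 0.72 × 0.28)] = 0.193.

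**3. Odds ratio with age.** The article gives no association between age and recovery, so a range is assumed: an odds ratio of 1.25 to 3 per SD of age, with age uniform. Over 6 months to 18 years one SD would be 17.5/√12 ≈ 5.1 years. For each arm, the intercept is solved so that the recovery probability averaged over age equals the stated rate; the difference between the two intercepts is the age-conditional log odds ratio. Standard errors and power come from 1,000 simulated trials of 488 children per scenario, site left out.

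At 60 % v 72 % (odds ratio without age 1.714):

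| Age OR per SD (assumed) | OR with age | Ratio to 1.714 | SE of log OR, without → with age | Power, without → with age |
|---|---|---|---|---|
| 1.25 | 1.725 | 1.01 | 0.194 → 0.196 | 81.6 → 82.6 % |
| 1.5 | 1.748 | 1.02 | 0.194 → 0.198 | 80.5 → 81.4 % |
| 2 | 1.813 | 1.06 | 0.194 → 0.205 | 81.2 → 84.8 % |
| 3 | 1.962 | 1.14 | 0.194 → 0.219 | 80.5 → 88.5 % |

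With an age odds ratio of 1, the two odds ratios coincide. Each simulated power carries a standard error of about √(0.8 × 0.2/1000) = 1.3 points, so differences of a point are close to noise, although both models see the same simulated data.

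**4. Scenarios nearer the later visits.** The Background gives 86 % v 72 % at 4 months in the one small paediatric trial, and 85 % at 6 months without steroids; the 95 % set against that 85 % is assumed. That trial did not use this trial's recovery definition, so these are illustrations only.

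- 72 % v 86 %: 2.39 without age; 2.41, 2.44, 2.55 and 2.78 with it. Power changes by 0 to about 1 point.
- 85 % v 95 %: 3.35 without age; 3.37, 3.41, 3.51 and 3.72 with it. Power changes by about 0 to 1 point.

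In every scenario with a prognostic age effect, adding age raises the standard error of the log odds ratio.

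**5. Linear models.** If age explains a share R² of the outcome variance, the standard error of the mean difference is multiplied by √(1 − R²). The article gives no R²; 5 to 10 % is assumed.

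- R² = 0.05: √0.95 = 0.975, about 2.5 % lower; equivalent to 1/0.95 = 1.05 times the sample.
- R² = 0.10: √0.90 = 0.949, about 5 % lower; equivalent to 1/0.90 = 1.11 times the sample.

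**The case against.** The strongest reply is that the remedy is largely planned already. The repeat analysis puts the primary and secondary outcomes on one covariate set that includes age, which is all that a like-for-like comparison needs. Differences in proportions are collapsible and are reported at each visit, so the course of the effect can be read from them. The plan nowhere proposes a formal comparison of odds ratios between visits. The sizes rest wholly on assumed age effects: at 1.5 per SD the gap on the log scale is about 0.02, against a standard error of 0.194, and the 95 % interval around 1.71 runs from about 1.17 to 2.5.

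Most of this stands, and it is why the point is minor. What it does not remove is the mismatch in the main estimates: the repeat is a supporting result and is conditional on three further covariates.

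Three stronger readings are tempting and not supported:

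- **That omitting age biases the secondary comparisons**, since the plan calls it a possible confounder. Allocation is randomised, site is the only stratification factor, and site is in all the main logistic and linear models.
- **That precision is lost in the odds ratios.** The table shows the reverse for the standard error; any gain there is in power.
- **That the age-dependent instruments and raters make the linear comparisons unsound.** Those changes are balanced between arms in expectation. They are also steps, which one linear age term would capture only in part.

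**Conclusion.** The inconsistency is in the text and is unexplained, but it is minor. The main HB odds ratios at 1 month and at 3 and 6 months are conditional on different covariates. The difference is nil if age is not prognostic, about 1 to 2 % in the odds ratio for an assumed age effect of 1.25 to 1.5 per SD, about 5 to 7 % at 2, and about 11 to 16 % at 3, across the three recovery scenarios. The article offers nothing to say which applies. A reader might infer that a trend in the odds ratios over the visits would be mainly an artefact of covariates; the figures do not support that unless age is strongly prognostic.

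The efficiency gain from age is real for the continuous outcomes if age explains some of their variance. For the binary outcomes it is a little power: roughly 1 to 8 points at 60 % v 72 % and at most about 1 point in the later-visit scenarios. Neither the validity of any comparison nor the sample size is affected.

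**What to change.** In Statistical analysis, adjust the main logistic and linear models for all secondary outcomes for site and age, with age continuous and in the same form as in the primary model. Keep the differences in proportions and the fuller adjusted repeat as planned. If site-only models are preferred for the secondary outcomes, state the reason.

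The cost is a wording change and one degree of freedom per model. No new data are needed, and the sample size stays as it is.

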### Ethics and dissemination

#### Research ethics approval

The trial has full ethics approval at the central study site from the Royal Children’s Hospital (RCH) Human Research Ethics Committee (HREC reference number RCH HREC/15/RCHM/V4). RCH HREC is also the central site for the National Ethics Application Form. The study has ethics and governance approval at all 10 sites.

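### The Cox model for time to recovery states no site term, although randomisation is stratified by site and the neighbouring models adjust for it

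*Protocol article*

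**What the plan says.** The protocol article's Randomisation section states: "An independent statistician has generated a randomization schedule using variable block sizes, stratified by site". Allocation is 1:1, and the Research ethics approval section gives 10 sites.

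The Statistical analysis section names site for three kinds of between-arm model:
- primary outcome: "odds ratio from a logistic regression model adjusted for site and age";
- binary secondary outcomes: "odds ratios from logistic regression adjusted for site";
- continuous outcomes: "comparisons made using linear regression adjusted for site presented as mean differences".

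The next sentence covers time to recovery: "Time to recovery will be assessed using a Cox proportional hazards model censoring patients who have not recovered at 6 months". It goes on to the reported quantities (hazard ratio, interval, p-value) and names no covariate or stratum. For the primary and secondary outcomes the section then says "we will repeat the analysis adjusted for age (as a continuous variable), gender, baseline severity of facial nerve dysfunction", followed by time to treatment. Site is not in that list.

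Time to complete recovery appears at the end of the Background, among questions the study will also inform, and in Statistical analysis. It is not in the Secondary outcomes list.

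**The concern.** An analysis should normally reflect the factor used to restrict randomisation. The article follows that rule for every other regression comparison of the arms and departs from it, without a reason, for one.

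Two consequences follow if sites differ in how fast children recover. A Cox hazard ratio that leaves out a prognostic factor lies nearer 1 than the ratio within levels of that factor. The model-based standard error also takes no credit for the balance that stratified allocation created.

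Some site variation is plausible from the article: diagnosis follows local guidelines, and the 1-month assessor's specialty depends on local resources. The Background reads the one paediatric randomised trial as suggesting that steroids speed recovery, and this analysis addresses that question most directly. Its hazard ratio would also be on a different conditional basis from the site-adjusted odds ratios beside it.

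**Working it through.** **Plan's own figure.** For 60% v 72%, two-sided alpha 0.05 and 80% power, the pooled-variance formula without continuity correction gives 244 per group (power 80.1%), as the Sample size estimation section states. The article gives no event count or power for the Cox analysis.

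**Inputs from the article.** 60% and 72% recovered at 1 month, 244 analysed per group, 10 sites, 1:1 allocation within site, censoring at 6 months.

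**Assumptions, not in the article.** Exponential recovery times observed exactly, equal site sizes, and a between-site SD of the log hazard from 0 to 0.8.

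**Implied hazard ratio.** ln(1 − 0.72) / ln(1 − 0.60) = ln 0.28 / ln 0.40 = 1.39.

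**Analytic check with no site variation.** The placebo hazard is −ln 0.40 = 0.916 per month. Expected events by 6 months are 244 × (1 − e^(−6×0.916)) + 244 × (1 − e^(−6×0.916×1.39)) = 486.9. Schoenfeld power is Φ(√(486.9/4) × ln 1.39 − 1.96) = 95.2%. The simulated value is 94.8%.

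**What each SD means.** A site z SDs from average has 1-month placebo recovery of 1 − 0.40^exp(z × SD). With z = ±1.96 this gives the central 95% of sites.

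**Simulation.** 488 children, permuted blocks within site, 2000 runs per row, true within-site HR 1.39. Each pair is Cox without site v Cox stratified by site.

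| Site SD | Site placebo recovery at 1 month | HR | Power (%) | Rejection under the null (%) |
|---|---|---|---|---|
| 0 | 60% | 1.39 v 1.39 | 94.8 v 93.8 | 4.6 v 4.6 |
| 0.2 | 46–74% | 1.37 v 1.39 | 93.4 v 93.8 | 5.4 v 5.4 |
| 0.3 | 40–81% | 1.36 v 1.39 | 92.0 v 93.0 | 4.4 v 5.6 |
| 0.5 | 29–91% | 1.32 v 1.39 | 86.2 v 92.2 | 3.8 v 5.4 |
| 0.8 | 17–99% | 1.27 v 1.39 | 76.0 v 93.0 | 1.4 v 5.6 |

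Simulation error is √(0.93 × 0.07 / 2000) = 0.6 points on a power of 93%, and √(0.05 × 0.95 / 2000) = 0.5 points on a 5% rejection rate. The conservatism is therefore clear only from SD 0.5 upward.

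**Smaller true effect.** With HR 1.25, where absolute power is lower, the differences are larger. Power without v with site strata is 69.6% v 66.2% at SD 0, 63.8% v 67.8% at SD 0.3, and 54.6% v 66.1% at SD 0.5.

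**Second simulation.** 486 children, site effects drawn from a normal distribution, 400 runs, HR 1.39:
- SD 0: power 94% v 93%.
- SD 0.3: HR 1.37 v 1.40, power 93% v 93%.
- SD 0.5: HR 1.34 v 1.40, power 89% v 94%.
- SD 0.7: HR 1.29 v 1.39, power 83% v 93%. The mean model-based SE without site was 0.092 against an empirical SD of 0.084, a ratio of 1.10.

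At SD 0.5 the two simulations put the power loss at 92.2 − 86.2 = 6 and 94 − 89 = 5 points.

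**The case against.** **The sentence is silent rather than specific.** It does not say unadjusted or treatment only. A reader might infer that the sponsor chose a Cox model without site, but the text does not show that. The article condenses a fuller protocol, and an analysis plan may add site. This stands as a limit on how firmly the point can be put. It does not remove the point, because the article does not defer site adjustment: it states it for the three other model types and omits it for this one.

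**The repeat is ambiguous.** The added covariates may replace site or join it. Even on the second reading, the stated Cox model has no site term to carry forward.

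**The effect needs large site differences.** This stands. SD 0.5 means 1-month placebo recovery from about 29% to 91% across sites. Nothing in the article suggests that spread in one research network with common eligibility criteria and centrally organised training.

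**The hazard ratio is not biased in the usual sense.** This also stands. The gap is non-collapsibility, not confounding: the model without site estimates a marginal ratio. A reader might infer an invalid test or excess false positives, but the simulations show the reverse.

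**The simulated data are cleaner than the trial's.** House-Brackmann grades are taken at 1, 3 and 6 months, and resolution dates are as perceived by parents, so times will be tied or recalled. The exponential model also has almost every placebo child recovered by 6 months, whereas the article cites 85% without steroids in the one paediatric trial. The absolute powers should not be carried over to the trial.

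**Conclusion.** The point holds as a minor inconsistency in what the article fixes: the Cox model is the one between-arm regression with no stated site term. If it is run that way and sites differ, the test stays valid but conservative, and the hazard ratio is marginal and nearer 1 than the within-site ratio. At the implied HR of 1.39 the power loss is about 1 point or less at site SD 0.3 and about 5 to 6 points at SD 0.5. If the true effect is smaller it can be larger: 67.8 − 63.8 = 4 points at HR 1.25 and SD 0.3. These sizes rest on an assumed site SD, equal sites and exactly observed exponential times.

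A reader might take the losses of 10 points (SD 0.7) or 17 points (SD 0.8) as the expected cost. The documents do not support that, since such SDs imply placebo recovery from about 21% to 97%, or 17% to 99%, across sites. Nor is a primary or listed secondary outcome weakened: the primary model adjusts for site, and time to recovery is supportive.

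**What to change.** In the Statistical analysis section, state that the Cox model for time to recovery is stratified by site, or includes site as a covariate to match the other models. State also that site is kept when the analysis is repeated with age, gender, baseline severity and time to treatment. If the analysis plan already says this, aligning the two documents is enough. The wording should be settled before unblinding so that the choice is clearly prespecified.

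No new data are needed. If sites do not differ, stratifying costs about 1 power point at HR 1.39 (94.8 − 93.8 = 1.0; 94 − 93 = 1 in the second simulation). At HR 1.25 the cost was somewhat more (69.6 − 66.2 = 3.4 points).

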### Outcomes

#### Primary outcome

The primary outcome is complete recovery at 1 month post randomisation, where recovery is defined as a House Brackmann score of 1 [18, 27]. Recovery will be assessed face-to-face by a site specialist clinician who may be a pediatric neurologist, ear-nose-throat (ENT) specialist, pediatrician or ED physician. Where the participant is unable to attend the study site, it may be completed via videoconference using an online tool.

There are several different tools used in studies to describe the degree of facial dysfunction of Bell’s palsy, including the House Brackmann (HB) [12, 18, 19, 29–31], Sunnybrook [19, 32], Facial Paralysis Recovery Index/Profile [29, 33], and Yanagihara grading systems [34, 35]. The two largest adult RCTs used Sunnybrook scale and HB scale, or the HB scale alone [18, 19], and the only RCT of steroids for treating Bell’s palsy in children from Unüvar et al. [12] used the HB scale to assess recovery. In line with these studies, the primary tool to determine outcome in this study is the HB scale as used slightly modified by Sullivan et al. [36].

Using the HB scale, the two largest adult studies defined recovery as reaching a HB grade of 1 (HB 1) [18, 19]; others, including Unüvar [12], used HB grade 1 or 2. Sullivan et al. [18] initially set ‘complete recovery’ at HB grade 1 or 2, however, very early in the study the investigators found that participants only looked and felt fully recovered once HB grade 1 was obtained and hence changed their definition to HB grade 1. Our study accordingly defines full recovery as having achieved HB grade 1.

There are currently limited data regarding how long it takes children to recover from Bell’s palsy but existing data suggest a more rapid recovery in children than in adults [4, 12, 14, 37]. Unüvar’s study of 42 children [12] found that 72 % of children had complete recovery at four months, 85 % at six months, and 100 % recovery at 12 months without steroids. In two paediatric observational studies [4, 14], the mean time to recovery was five weeks (range 1–21 weeks) and 59 % had recovered at 1 month without steroids. Therefore the primary outcome in the current study was chosen as complete recovery at 1 month with recovery at 3 and 6 months as secondary outcomes.

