### Study procedures

An overview and the timing of the study procedures are outlined in detail in Table 2.

**Table 2 Tab2:** Assessment Schedule BellPIC Study

Procedure	Enrolment & Randomisation Time point 1	Time point 2	Time point 3	Time point 4	Time point 5	Time point 6
	Day 1	Day 14^a^	Month 1^b^	Month 3^b^	Month 6^b^	Month 12^d^
Obtain Informed consent	✓					
Collect demographic and relevant information	✓					
Facial images	✓		✓	✓	✓	
House Brackmann [18, 27] & Sunnybrook [32, 38] scales augmented with SAQ [48]	✓		✓	✓	✓	
Review inclusion & exclusion criteria	✓					
Randomise	✓					
Study drug dispense	✓					
Study drug compliance review		✓	✓			
Adverse events review		✓	✓^e^			
Specialist clinician review			✓^c^			
Emotional and functional impact using PedsQL, CHU-9D and Harter scales [39–44]			✓	✓	✓	
Assessment of pain (VAS/FPS-R) [45–47]			✓	✓	✓	
Participant and parent perception of recovery (lay translation of HB scale)		✓	✓	✓	✓	✓
Collection of information on medical attendances			✓	✓	✓	

*HB* House Brackmann scale, *SAQ* Synkinesis Assessment Questionnaire, *PedsQL* Pediatric Quality of Life inventory, *CHU-9D* Child Health Utility 9D, *VAS* Visual Analogue Scale, *FPS-R* Faces Pain Scale Revised

^a^This assessment will be conducted over the telephone or on-line. A window of ±5 days is allowed

^b^A window of ± 7 days will be allowed to facilitate appointment scheduling for the study assessments attended on-site at 1 month; a window of ±14 days will be allowed to facilitate appointment scheduling or follow up contacts by phone, email or online for study visits or contacts at 3 and 6 months. Once a participant has been assessed to have made a complete recovery (HB score of 1), they will no longer be required to attend further visits to the study clinic and will only be required to complete questionnaires and scales by telephone, email or online at 3 and 6 months

^c^The senior specialist clinician may be a pediatric neurologist; ENT specialist; pediatrician; or ED physician

^d^This assessment will be required only for those deemed to have been not recovered at their 6 month assessment. A window of ±14 days will be allowed to facilitate follow up contacts scheduling

^e^Adverse events which are unresolved at 1 month should be followed till resolution or stabilisation

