#### Follow up assessment at 3 and 6 months

A site research assistant will arrange a follow-up assessment for any participants deemed at their previous visit not to be fully recovered (HB score greater than 1). For participants unable to attend the study site, assessment will be conducted remotely as previously described.

Participants deemed to have fully recovered at the 1 month visit will not be required to attend the study site for the remaining study time points; the parent/guardian or participants (age dependent) will instead be asked to complete the questionnaires online or via mail (or via telephone, administered by the research assistant if required). The questionnaires will be the same as those completed by the unrecovered participants but without HB, Sunnybrook, SAQ scoring or facial imaging. Similarly, participants who have fully recovered at the 3 month visit will not be required to attend the study site for the 6 month time point and the parent/guardian/participant will instead be asked to complete the questionnaires online or via mail (or via telephone, administered by the research assistant if required).

Parent/guardian or participant questionnaires, grading scales and facial imaging will be performed similar to the 1 month visit (see Table 1).

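### Time to recovery is planned as an ordinary Cox analysis, but HB grade 1 is observed only at the 1, 3 and 6 month visits; if visit dates are used, a true effect is attenuated, and a grouped-time model avoids this

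*Protocol article*

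**What the plan says.** The planned method is in the Statistical analysis section of the protocol article: "Time to recovery will be assessed using a Cox proportional hazards model censoring patients who have not recovered at 6 months". The result is to be a hazard ratio with confidence interval and p-value. The following sentence treats children who recovered by the 1 or 3 month assessment, and were not assessed again, as recovered from then on.

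Under Primary outcome, "recovery is defined as a House Brackmann score of 1". The Background uses the same HB grade 1 definition and then names time to complete recovery among the further questions of the study. The Secondary outcomes list has no entry for time to recovery, so nothing there says which event or date is meant.

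Table 2 shows HB grading on day 1 and then at months 1, 3 and 6 only. Its footnote b sets the scheduling windows: "A window of ± 7 days will be allowed to facilitate appointment scheduling for the study assessments attended on-site at 1 month", and for the later visits "a window of ±14 days will be allowed to facilitate appointment scheduling or follow up contacts by phone, email or online".

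One calendar date is collected. The 1 month questionnaire asks for the "date of resolution of facial palsy symptoms (if resolved) as subjectively perceived by parent". For 3 and 6 months, "Parent/guardian or participant questionnaires, grading scales and facial imaging will be performed similar to the 1 month visit", so the item can be repeated. The article does not link this date to the Cox model.

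**The concern.** A child first graded HB 1 at the 1 month visit recovered at some unknown time before it. A child graded above 1 at 1 month and 1 at 3 months recovered somewhere between the two. Under the planning rates, 60 % and 72 % of the two arms, about two thirds of all children, share the first interval. An ordinary Cox model needs an event time for each child. If the visit supplies it, most events are tied at nominal times or ordered by when the appointment happened to fall, and neither carries information about the speed of recovery.

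At stake is the hazard ratio for time to recovery. The Background reads the one small paediatric randomised trial as suggesting that steroids speed up recovery, so readers will look at this estimate.

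**Working it through.** **Inputs from the article.** Sample size estimation gives 60 % (placebo) and 72 % (prednisolone) recovery at 1 month, 244 per group for 80 % power at two-sided 0.05, and 270 per group recruited. Table 2 gives visits at 1, 3 and 6 months with windows of ±7, ±14 and ±14 days.

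**Assumed.** Placebo recovery of 70-90 % at 3 months and 85-97 % at 6 months; proportional hazards; actual visit dates uniform within the windows. The article's only anchor for the later rates is the small paediatric trial (72 % untreated recovery at 4 months, 85 % at 6 months).

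**The plan's own figure.** With mean proportion 0.66, n = [1.96·√(2·0.66·0.34) + 0.8416·√(0.60·0.40 + 0.72·0.28)]² / 0.12² = (1.313 + 0.559)² / 0.0144 ≈ 243.4, so 244 per group. This agrees with the article. It gives no figure for time to recovery.

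**True hazard ratio.** HR = ln(1 − 0.72) / ln(1 − 0.60) = ln 0.28 / ln 0.40 = 1.389.

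**One case by hand.** Take placebo recovery of 60, 75 and 85 % at the three visits. The proportions unrecovered are 0.40, 0.25 and 0.15 on placebo. Raised to the power 1.389 they are 0.280, 0.1457 and 0.0717 on prednisolone.

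- Grouped model: the ratio of log conditional survival is ln 0.28 / ln 0.40 = 1.389 in interval 1, ln(0.1457/0.28) / ln(0.25/0.40) = 1.389 in interval 2, and ln(0.0717/0.1457) / ln(0.15/0.25) = 1.389 in interval 3. The complementary log-log model estimates this quantity, so grouping does not distort it.
- Cox, Breslow ties, nominal visits: solve Σ[d₁ − (d₀ + d₁)·n₁h/(n₀ + n₁h)] = 0, where n is the proportion still at risk and d the proportion recovering in the interval. At h = 1.219 the three terms are 0.7200 − 0.7251, 0.1343 − 0.1309 and 0.0741 − 0.0723. They sum to zero within rounding. The share of the log hazard ratio lost is 1 − ln 1.219 / ln 1.389 ≈ 40 %.
- Cox, Efron ties, nominal visits: 1.355, a loss of about 8 %.

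**Over the assumed range** (100,000 simulated children per arm, true HR 1.389):

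| Placebo recovery at 3 / 6 months | Breslow, nominal | Efron, nominal | Breslow, dates in windows | Efron, dates in windows | Complementary log-log |
|---|---|---|---|---|---|
| 70 / 85 % | 1.215 | 1.349 | 1.341 | 1.354 | 1.383 |
| 75 / 85 % | 1.221 | 1.358 | 1.337 | 1.350 | 1.392 |
| 80 / 90 % | 1.212 | 1.356 | 1.331 | 1.344 | 1.393 |
| 85 / 95 % | 1.197 | 1.348 | 1.326 | 1.340 | 1.393 |
| 90 / 97 % | 1.178 | 1.326 | 1.317 | 1.331 | 1.381 |

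Events dated to the day give 1.37 to 1.40. With a true hazard ratio of 1, every visit-dated Cox fit gives about 1.00.

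**At trial size** (270 per arm; placebo recovery 75-85 % at 3 months and 85-95 % at 6 months):

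- Breslow at nominal visits: 1.20 to 1.22, 95 % interval coverage 69-81 %, power 53-60 %.
- Actual dates within the windows: 1.32 to 1.35, coverage 91-95 %.
- Complementary log-log: 1.37 to 1.41, coverage about 94-96 %, power 91-95 %.

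**The case against.** The strongest reply is that the article never says the visit date is the event date, nor that the Cox endpoint is HB grade 1. The HB definition quoted above belongs to the primary outcome. A calendar date is collected from parents, and an ordinary Cox model suits a recorded date. Tie handling and event dating are also details that a condensed article may leave to an analysis plan.

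Part of this stands. The article does not say that recovery dates are treated as exact, and the parent-perceived date could feed a Cox model. But that date is subjective, is not an HB grade, and is never connected to the analysis. The Background defines complete recovery as HB grade 1 before naming time to complete recovery, and the sentence after the Cox sentence deals in recovery status at 1 and 3 months. The natural reading is therefore visit-based. The model itself is stated, so this is a choice and not merely an omitted detail.

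Three stronger readings are tempting and are not supported.

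- **The hazard ratio is biased toward 1 whatever is done.** Size depends on the date source and on ties: dating to the day gives almost none. A discrete logistic fit, the exact-discrete type of tie handling, gives 1.65 to 1.76, further from 1, but that is an odds ratio.
- **The confidence intervals are too narrow.** In the worst case, Breslow at nominal visits, the model standard error is about 0.09 against an empirical standard deviation of about 0.055. The intervals are too wide, and coverage is lost through bias alone.
- **This is the only analysis bearing on speed.** Recovery at 1, 3 and 6 months also bears on it, and those binary comparisons are unaffected.

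**Conclusion.** The point holds in conditional form. HB-defined recovery is interval-censored by the visit schedule, and the stated model does not allow for that. If visit dates are the event times and prednisolone works as planned for, a hazard ratio of 1.39 is reported as about 1.32 to 1.36 with Efron ties or actual visit dates, a modest loss with near-nominal coverage. Only Breslow ties at nominal visit times give a large loss, to about 1.2.

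If the parent-perceived date is used instead, the attenuation goes but the endpoint is no longer HB grade 1. Either way the text needs to settle what is being timed.

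The figures rest on proportional hazards and on assumed 3 and 6 month recovery rates. There is no bias when there is no effect, and the primary outcome and sample size are untouched. This is an improvement to one secondary analysis, worth making because it is nearly free.

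**What to change.** State that the event in the time-to-recovery analysis is first attainment of HB grade 1. Analyse it with a discrete-time complementary log-log model over the intervals 0-1, 1-3 and 3-6 months, with treatment and site as covariates, and report the hazard ratio from that model. An interval-censored proportional hazards model is an equal alternative, and it copes directly with a child who misses the 3 month visit and is found recovered at 6 months. Keep any Cox analysis of the parent-perceived resolution date as a separate analysis labelled supportive.

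No new data are needed, only changed wording and standard software. The price is a slightly less familiar model and a slightly larger standard error than a visit-dated Cox fit.
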